**Figure 1 F1:**
[figure not shown]
Selection of study clusters.

The estimated number of pregnant women covered by the intervention is around 4800 which include approximately 110 pregnant women from each VDC of Bajhang and Dailekh as a mountain and hill district respectively inhabiting less number of population, and approximately 310 pregnant women from Kanchanpur as a terai district with densely-populated lowland.

### Sample size estimate

The study includes all pregnant women in the 36 VDCs. It is estimated that at least 110 births per year will occur in each VDC and that the proportion of births assisted by a SBA is 36% [7]. The sample size was estimated assuming that the intervention and control groups and the unmatched clusters were of approximately equal size. A value of k -the between-cluster coefficient of variation – to be equal was estimated in the intervention and control groups. All estimates are based on a two-tailed 5% significance level. The value of k is likely to be 0.25 on the basis of estimates of the SBA utilization rate according to the baseline survey [24]. Hence, It was estimated that on at least 110 pregnant women in each cluster with 36 clusters would be required for the period of one year to detect a 10% difference in SBA utilization rate with 80% power and 95% confidence level.

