### Study design

The implementation research underway is to test the impact of interventions designed to address the main barriers to utilization of SBA services at birth identified in the baseline study. The study design is a cluster randomized controlled trial. The three districts (Bajhang, Dailekh and Kanchanpur) were the three strata and the VDCs from each stratum serve as clusters which were allocated for intervention and control by *randomization*. A baseline survey was conducted in 2011 in all 50 VDCs of the three districts. All women with under-5 children from each VDCs were included.

The three districts of Far and Mid-west Nepal represent three ecological zones –- Kanchanpur is Terai or a lowland belt stretching east to west in the south; Dailekh is Hills; and Bhajang is a mountainous areas. Selection of three districts was based on ecology with low human development index. The population inhabiting these districts is varied, representing different ethnic groups [31]. Terai district is mainly inhabited by aboriginal population of Nepal the Tharus; the mid hills by Kshetri and Bahun (Aryan upper cast but lower economic status). The mountain district has predominantly Mongoloid populations. These districts have lower indicators with respect to education, health and economic development.

The implementation of intervention covers 36 of the 50 VDCs of the three districts (22 VDCs of Bajhang, 10 VDCs of Dailekh and 4 VDCs of Kanchanpur (see table in Figure 1). VDCs having a rate of utilization of SBA at birth higher than the national target of 60% were excluded from the intervention. In order to have an even number of clusters, one more VDC with coverage of 57% was excluded.

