### Analysis strategies

Data will be double entered into EpiData 3.1, validated using Epi Info data compare, and will be transferred to SPSS 16 for analysis. The findings from quantitative tool will be presented in tabular and graphical forms. To control for more than one confounding variable multivariate logistic regression model will be applied. For statistical inference of the result, a confidence level of 95% is set. For the analysis process of qualitative data collected form FGD, the transcription of taped FGD session will be typed and reviewed thoroughly then translated in English language by field coordinators. The content of transcription will then be labeled as per the domain of analysis.

Missing data will be characterized in terms of the degree and patterns of missing data. For imputation of missing value of categorical variables, the frequency distribution will be used as the basis for randomly generating a value for each observation lacking a response. For example, if education was measured in three categories -- “less than high school” (25% of complete data cases), “completed high school” (40%), or “more than high school” (35%) -- then for each observation with education missing, a random number between 0 and 1 will be drawn from a uniform distribution and the missing value replaced with “less than high school” if the random number is less than or equal to 0.25, “completed high school” if the number is greater than 0.25 but less than or equal to 0.65, or “more than high school” if greater than 0.65. For imputation of numerical variable regression method is used.

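### The sizing assumes VDCs of about equal size, but four are nearly three times the rest; at the planned sizes power is about 74–76% if VDCs count equally and 67–69% if women do (with a clustered standard error), against the stated 80%

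*Protocol article*

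**What the plan says.** - **Sizing assumption** (Protocol article, Sample size estimate): "The sample size was estimated assuming that the intervention and control groups and the unmatched clusters were of approximately equal size". The same section takes at least 110 women in each of 36 clusters and concludes that this is enough "to detect a 10% difference in SBA utilization rate with 80% power and 95% confidence level".
- **Sizing inputs** (same section): "the proportion of births assisted by a SBA is 36"%, "The value of k is likely to be 0.25 on the basis of estimates of the SBA utilization rate according to the baseline survey", and "All estimates are based on a two-tailed 5% significance level". The coefficient k is taken as equal in the two arms.
- **Planned clusters** (Study design): "22 VDCs of Bajhang, 10 VDCs of Dailekh and 4 VDCs of Kanchanpur", with districts as strata.
- **Planned sizes** (Study design, text after Figure 1): about 110 women in each Bajhang and Dailekh VDC, and "approximately 310 pregnant women from Kanchanpur as a terai district with densely-populated lowland", for a total of around 4,800.
- **Analysis** (Analysis strategies): "To control for more than one confounding variable multivariate logistic regression model will be applied". No method for clustering is named. The Project time line section says that intervention and control VDCs will be compared with an appropriate test; it fixes neither the unit of analysis nor the weights.

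**The concern.** The protocol had the expected cluster sizes when it was written, and its sizing assumption does not match them: a Kanchanpur VDC is about 2.8 times the size of the others (310/110).

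Whether this matters depends on how VDCs are weighted. At k = 0.25 most of the variance of a VDC's proportion lies between VDCs, so 200 extra women in one VDC add little information. An ordinary logistic regression nevertheless counts each woman once, which gives 4 of 36 VDCs (11%) a weight of 1,240/4,760 = 26%.

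The practical risk lies in the repair. The named model needs an allowance for clustering, and the quickest one is to add a cluster-robust standard error and leave the weights alone. That largely corrects the type I error but gives away power that a different weighting would keep, in a trial whose own inputs already fall short of 80%.

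**Working it through.** **Inputs.** From the sample size section: control proportion 0.36; a 10% difference, read as a rise of 10 points to 0.46; k = 0.25 in both arms; 18 VDCs per arm; two-sided 5%. From the study design section: 32 VDCs of 110 and 4 of 310. Assumption: the Kanchanpur stratum splits evenly, so each arm has 16 VDCs of 110 and 2 of 310 (2,380 women).

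**1. The 310 is per VDC.** 32 × 110 + 4 × 310 = 4,760, which fits the stated 4,800. As a district total it would give 3,520 + 310 = 3,830, which does not.

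**2. The plan's own figure, equal VDCs of 110.** The usual formula for unmatched clusters is

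c = 1 + (1.96 + 0.842)² × [p₀(1−p₀)/n + p₁(1−p₁)/n + k²(p₀² + p₁²)] / (p₁ − p₀)²

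The bracket is 0.2304/110 + 0.2484/110 + 0.0625 × (0.1296 + 0.2116) = 0.00435 + 0.02133 = 0.02568. So c = 1 + 7.849 × 0.02568/0.01 = 21.15, or 22 VDCs per arm against 18 planned. Power at 18 is Φ(√(17 × 0.01/0.02568) − 1.96) = Φ(0.613) = 73.0%, or 75.4% without the added 1. The stated 80% is not reproduced; it needs k of about 0.225 (0.233 without the added 1). A between-VDC standard deviation of 0.09 in both arms gives 82.0%, but the section says that k, not the standard deviation, is equal.

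**3. Planned sizes.** With weights wᵢ summing to 1, the variance per arm is Σ wᵢ² [(kp)² + p(1−p)/nᵢ].

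*Women weighted equally, clustered standard error* (wᵢ = nᵢ/2,380):
- Σ wᵢ² = (16 × 110² + 2 × 310²)/2,380² = 385,800/5,664,400 = 0.0681, or 14.7 effective VDCs per arm instead of 18.
- Control: 0.0081 × 0.0681 + 0.2304/2,380 = 0.000649. Intervention: 0.013225 × 0.0681 + 0.2484/2,380 = 0.001005.
- SE = √0.001654 = 0.0407. Power = Φ(0.1/0.0407 − 1.96) = 69.1%, or 66.6% with the small-sample factor 17/18.

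*VDCs weighted equally* (wᵢ = 1/18; mean of 1/nᵢ = 0.00844):
- Control: (0.0081 + 0.2304 × 0.00844)/18 = 0.000558. Intervention: (0.013225 + 0.2484 × 0.00844)/18 = 0.000851.
- SE = √0.001409 = 0.0375. Power = 75.9%, or 73.5% with the same factor.

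*Inverse-variance weights*, which a random-intercept model approximates: 76.0%, or 73.6%.

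**4. Sensitivity to k** (normal approximation, planned sizes):

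| k | VDCs equal | Women equal | Loss (points) |
|---|---|---|---|
| 0.15 | 97.5% | 96.05% | about 1.5 |
| 0.20 | 89.1% | 84.5% | 4.6 |
| 0.25 | 75.9% | 69.1% | 6.8 |
| 0.30 | 62.4% | 55.1% | 7.3 |

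At k = 0.25 with the small-sample factor, the woman-weighted loss is 6.4 points against 36 equal VDCs of 110 (73.0%) and 7.6 against equal VDCs of the mean size, 132 (74.2%).

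**5. Simulation** (beta-binomial, 20,000 runs, k = 0.25, planned sizes). The t test on VDC proportions has 73.9% power. The woman-weighted test with a robust standard error has 69.4%, with a type I error of 5.6%; that slight excess flatters its power. A woman-level test with no correction has a type I error of 44%.

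**The case against.** **The loss is not a property of the analysis as written.** A reader might infer that the stated logistic regression loses about 7 points of power. It does not. Run literally, with no allowance for clustering, its standard error is too small and it rejects too often; its fault is type I error, which is a separate matter. The 7 points arise only if women keep equal weight and the standard error is corrected. This stands, and the point is conditional for that reason.

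**The sizing is not harmed by unequal size as such.** A formula based on k corresponds to a comparison of VDC proportions, and 110 is a minimum. On that comparison the four larger VDCs move power from 75.4% to 75.9%, slightly up. This stands too.

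**Weighting may be left to a fuller document.** A condensed article can leave this open. But the equal-size assumption and the 80% are stated figures that conflict with the plan's own sizes and inputs, and the one model named is at woman level.

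**Weighting by women is legitimate.** It targets the average over women, which suits an outcome defined as women's use of the service. That is a fair reason to report it, at a known price in power.

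**Kanchanpur's baseline coverage.** A reader might add that the heavily weighted district has 64% coverage at baseline. That figure covers the surveyed district, whereas the design then excluded VDCs above 60%. It does not describe the four trial VDCs, and nothing here rests on it.

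**Conclusion.** The point holds in conditional form. The equal-size assumption conflicts with the planned sizes. At those sizes and k = 0.25, power is about 74–76% with VDCs counting about equally, and about 67–69% with women weighted equally and a clustered standard error. Both are below 80%. Most of the first shortfall comes from the stated inputs and is there with equal VDCs as well (73.0–75.4%); it should not be charged to unequal size.

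The conditional loss is about 7 points at k = 0.25, about 5 at 0.20 and 1–2 at 0.15; in the simulation at k = 0.25 it was 4.5 points. It is fully recoverable by the choice of weights. The figures assume a 10-point rise, equal k in both arms and two Kanchanpur VDCs per arm. They ignore the district strata, and adjusting for district could reduce the variation between VDCs and raise power under either weighting.

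**What to change.** **Analysis strategies.** Fix the primary comparison as one of:
- VDC-level proportions of births with a skilled attendant, 18 versus 18, compared within district; or
- a logistic model with a VDC random intercept and district as a fixed effect, noting that this gives a conditional odds ratio.

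Report the woman-weighted estimate with a cluster-robust standard error as a sensitivity analysis.

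**Sample size estimate.** Replace the equal-size assumption with the actual sizes (32 VDCs of about 110, 4 of about 310). Restate the power for that mix and the chosen weighting: about 74–76% at k = 0.25, before any gain from the strata, in place of 80%.

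**Cost.** Wording only; no extra women, VDCs or data. The downside is that a VDC-level estimate averages over VDCs rather than women. That suits a package which the protocol describes as acting on the health system rather than on individuals, and the sensitivity analysis keeps the average over women in view.

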**Method/Design:**

This study involves a cluster randomized controlled trial involving approximately 5000 pregnant women in 36 clusters. The 18 intervention clusters will receive the following interventions: i) mobilization of family support for pregnant women to reach the health facility, ii) availability of emergency funds for institutional childbirth, iii) availability of transport options to reach a health facility for childbirth, iv) training to health workers on communication skills, v) security provisions for SBAs to reach services 24/24 through community mobilization; 18 control clusters will not receive the intervention package. The final evaluation of the intervention is planned to be completed by October 2014. Primary study output of this study is utilization of SBA services. Secondary study outputs measure the uptake of antenatal care, post natal checkup for mother and baby, availability of transportation for childbirth, operation of emergency fund, improved reception of women at health services, and improved physical security of SBAs.

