Our project baseline during April to December 2012 in Bajhang, Dailekh and Kanchanpur districts of Mid and Far Western Development region in collaboration with GoN and financial and technical support form WHO Geneva reported first ANC coverage of 88% while 4^th^ and more ANC visit of 65% in average. Only the half of the respondents (52%) knew about danger signs during pregnancy and delivery and 19% of them had faced complications during last delivery.

Our survey reported, 45% of births were assisted by SBA/THW which ranges from a high of (64%) in Kanchanpur and a low of (33%) in Bajhang. Which is low as compared to MDG target to scale up SBA coverage to 60% by 2015 [13]. This suggests additional efforts are required in scaling up skilled birth attendants in Nepal. This requires innovative intervention that uniquely address identified barriers in receiving care. Distance to reach health facility, lack of transportation means to reach the health facility, lack of information about the availability of services in health facilities were the identified barriers.

Amidst of possibilities and challenges in SBA service scale up, Nepal Public Health Foundation (NPHF) [24] has taken initiative and has been conducting a study on “Overcoming Barriers to Scaling Skilled Birth Attendants Utilization in Improving Maternal, Newborn and Child health in Nepal” as a three-year implementation research project with support from WHO-HQ, Geneva. The overall aim of the implementation research is to increase SBA service utilization by identifying the barriers related to service users and health systems regarding the utilization of skilled birth attendants and implementing a package of interventions to address these barriers.

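### On the article's own inputs, 18 VDCs per arm give about 73–75% power for 36% versus 46%, not the stated 80%

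*Protocol article*

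**What the plan says.** The Sample size estimate section of the protocol article gives a complete set of inputs.

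- Cluster size: "It is estimated that at least 110 births per year will occur in each VDC".
- Control rate: "the proportion of births assisted by a SBA is 36" per cent, taken from a cited source.
- Between-cluster variation: "The value of k is likely to be 0.25 on the basis of estimates of the SBA utilization rate according to the baseline survey". The section takes k as equal in the two groups.
- Design: unmatched clusters of roughly equal size, tested two-sided at 5%.
- Result: 110 women per cluster "with 36 clusters would be required for the period of one year to detect a 10% difference in SBA utilization rate with 80% power".

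The abstract splits the 36 clusters evenly, 18 to intervention, and "18 control clusters will not receive the intervention package".

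Two other places bear on the inputs. The Background reports from the project's own survey that "45% of births were assisted by SBA/THW which ranges from a high of (64%) in Kanchanpur and a low of (33%) in Bajhang". The text with Figure 1, under Study design, expects about 110 women per VDC in Bajhang and Dailekh but "approximately 310 pregnant women from Kanchanpur as a terai district".

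**The concern.** Unmatched clusters, a common k, a stated cluster size and a two-sided 5% test are exactly the inputs of the standard formula for unmatched cluster trials of proportions. Put into it, they do not return 36 clusters at 80% power.

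The power figure shapes how a null result is read. The article says the Ministry of Health will scale up the package if it is proven effective, so a non-significant result has policy weight. On the stated inputs the chance of missing a true 10-point gain is about 25–27% (23–27% if larger mean cluster sizes are allowed for), where the article promises 20%. A reader cannot see this without redoing the calculation.

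**Working it through.** **Inputs.** p0 = 0.36, p1 = 0.46 (10% read as percentage points, in the direction of the primary objective), m = 110, k = 0.25 in both arms, two-sided 5%, all from Sample size estimate; 18 VDCs per arm from the abstract.

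**Formula.** With V = p0(1 − p0)/m + p1(1 − p1)/m + k²(p0² + p1²),

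- VDCs per arm: c = 1 + (1.96 + 0.842)² × V / (p1 − p0)²
- power at c per arm: Φ(√[(c − 1)(p1 − p0)²/V] − 1.96)

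**Attempt to reproduce the stated figure.**

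- Binomial part: 0.2304/110 + 0.2484/110 = 0.00435
- Between-cluster part: 0.0625 × (0.1296 + 0.2116) = 0.02133
- V = 0.02568
- c = 1 + 7.849 × 0.02568/0.01 = 21.15, so 22 per arm (44 VDCs), not 18 (36)
- Power at 18 per arm: Φ(√(17 × 0.01/0.02568) − 1.96) = Φ(0.613) = 73.0%

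**Variants that keep the stated assumptions.**

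| Variant | Power at 18 per arm |
|---|---|
| Formula as above | 73.0% |
| Without the +1 | 75.4% |
| Noncentral t, 34 df | 73.0% |
| Noncentral t, 30 df | 72.6% |
| m = 132, with / without the +1 | 74.2% / 76.6% |
| m = 139, with / without the +1 | 74.5% / 76.9% |

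The size of 132 is (32 × 110 + 4 × 310)/36 = 4760/36; 139 is 5000/36. None of these reaches 80%. The difference detectable with 80% power at 18 per arm of 110 is 11.0 points (10.7 without the +1). Holding 36% versus 46%, 80% is reached only if k is at most about 0.225 (0.233 without the +1).

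**How 36 can be recovered.** Let k = 0.25 describe the control arm only and let both arms share its standard deviation, 0.25 × 0.36 = 0.09 (so k = 0.09/0.46 = 0.196 under intervention).

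- V = 0.00435 + 2 × 0.0081 = 0.02055
- c = 1 + 7.849 × 0.02055/0.01 = 17.13, so 18 per arm, with power 82.0%

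A design-effect calculation lands close by. The intracluster correlation is k²p0/(1 − p0) = 0.0625 × 0.36/0.64 = 0.035, and c = 16.65 (17.53 with continuity correction). Leaving out the binomial part altogether also rounds to 18: 1 + 7.849 × 0.02133/0.01 = 17.74. The article does not say which route, if any, was used.

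**Sensitivity to the control rate.**

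- 45% versus 55%, k = 0.25: V = 0.0045 + 0.0625 × (0.2025 + 0.3025) = 0.03606; power 58.4%
- 45% versus 55%, k = 0.20 (the same control-arm standard deviation of 0.09): V = 0.0045 + 0.04 × 0.505 = 0.0247; power 74.6%

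The article gives no rate for the 36 retained VDCs (22 Bajhang, 10 Dailekh, 4 Kanchanpur). As an illustration, assume Bajhang at 33% and Kanchanpur at 60% after exclusions, with Dailekh unknown:

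| Dailekh (assumed) | Mean of the 36 VDCs | Power for +10 points, k = 0.25 |
|---|---|---|
| 33% | 36.0% | 73% |
| 38% | 37.4% | 71% |
| 60% | 43.5% | 61% |

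**The case against.** The best defence is that 36 clusters follow exactly from a reasonable assumption, a common between-cluster standard deviation, and that power is then 82%. The arithmetic is right. It cannot stand beside the statement that k is equal in the two groups, however, because a common standard deviation means a smaller k where the rate is higher. One of the two must go.

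It can also be said that the shortfall is modest: about 5 to 7 points of power, an 11-point rather than a 10-point detectable difference, and a k described only as likely. The calculation also ignores any gain from stratifying by district. All of that is fair and bears on size. It does not make 80% follow from the inputs. The gain from district or baseline adjustment cannot be counted on either, because no within-district k is given.

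Several stronger readings are tempting and not supported:

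- *Power is really 58%, because the trial's baseline is 45%.* The 45% counts births attended by an SBA or THW and averages the survey before VDCs above 60%, and one at 57%, were excluded. Of the 36 retained VDCs, 22 are in Bajhang, reported at 33%, so 36% is plausible. The 58% also carries k = 0.25 unchanged to a higher rate.
- *The within-VDC variance must have been left out.* That route gives 18 per arm, but so does the common standard deviation with that variance kept.
- *The chance of missing the effect is at least 27%.* It is 23–26% without the +1 or at the mean size of 132, and 110 is stated as a minimum.
- *The 10% may be relative.* Beside a rate of 36%, an absolute difference is the natural reading, though the word should be added.
- *Unequal cluster sizes make matters worse.* Only 4 of 36 VDCs are large. If VDCs are weighted equally, as the formula assumes, their size raises power slightly.

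**Conclusion.** The stated 80% does not follow from the stated inputs. With 36% versus 46%, k = 0.25 in both arms, 110 births per VDC and a two-sided 5% test, 18 VDCs per arm give 73% power, 75% without the +1 correction and 74–77% at a mean size of 132. Reaching 80% takes about 22 per arm, or a difference of about 11 points. The paragraph is internally consistent only if k = 0.25 is confined to the control arm, which its own equal-k statement rules out.

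This rests on reading 10% as absolute and on the standard unstratified formula, which the section's wording describes. Power at the true baseline of the retained VDCs cannot be computed from the article. The defect is a moderate overstatement of power. It does not show that the trial is too small to be useful.

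**What to change.** Amend the Sample size estimate section in one of two ways:

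1. State that 18 VDCs per arm of about 110 births give about 73–75% power for an absolute 10-point difference (36% versus 46%, k = 0.25 in both arms), or 80% power for about 11 points.
2. If a common between-cluster standard deviation was intended, say so, give its value (0.09), and withdraw the statement that k is equal in the two groups.

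In either case, label the 10% as absolute. Recompute with the baseline coverage and k of the 36 retained VDCs, within district, from the survey data already in hand, and note the unequal sizes (about 110 versus 310). Give 45% versus 55% only as a sensitivity figure (58% power at k = 0.25, about 75% at k = 0.20), with the reason that 45% is the SBA/THW average before exclusions.

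The cost is a rewritten paragraph, a short recalculation and, under the first option, a slightly less favourable stated power. No VDCs or women need be added.
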